# Efficacy and safety of Gantong Granules in the treatment of common cold with wind-heat syndrome: study protocol for a randomized controlled trial

**DOI:** 10.1186/s13063-015-0735-9

**Published:** 2015-05-19

**Keywords:** Common cold, Wind-heat syndrome, Gantong Granules, Randomized controlled trial, Traditional Chinese medicine

## Abstract

**Background:**

Although the common cold is generally mild and self-limiting, it is a leading cause of consultations with doctors and missed days from school and work. In light of its favorable effects of relieving symptoms and minimal side-effects, Traditional Chinese Medicine (TCM) has been widely used to treat the common cold. However, there is a lack of robust evidence to support the clinical utility of such a treatment. This study is designed to evaluate the efficacy and safety of Gantong Granules compared with placebo in patients with the common cold with wind-heat syndrome (CCWHS).

**Methods/Design:**

This is a multicenter, phase IIb, double-blind, placebo-controlled and randomized clinical trial. A total of 240 patients will be recruited, from 5 centers across China and randomly assigned to the high-dose group, medium-dose group, low-dose group or placebo control group in a 1:1:1:1 ratio. All subjects will receive the treatment for 3 to 5 days, followed by a 7-day follow-up period. The primary outcome is the duration of all symptoms. Secondary outcomes include the duration of primary symptoms and each symptom, time to fever relief and time to fever clearance, change in TCM symptom score, and change in Symptom and Sign Score.

**Discussion:**

This trial will provide high-quality evidence on the efficacy and safety of Gantong Granules in treating CCWHS, and help to optimize the dose selection for a phase III clinical trial.

**Trial registration:**

The registration number is ChiCTR-TRC-14004255, which was assigned by the Chinese Clinical Trial Registry on 12 February 2014.

## Background

The common cold has been with humanity since antiquity. It is the most widespread illness in humans with the average adult getting two to four colds a year and the average child getting six to eight colds [1]. Although the common cold is generally mild and self-limiting, it is the leading cause of consultations with doctors and days missed annually from school and work [2]. There are more than 200 viruses associated with the common cold and the rhinovirus is the most common cause [3]. The symptoms of the common cold can vary considerably between different viruses and often include a tickle or sore throat, sneezing, runny nose, nasal congestion, coughing, mild fever and general malaise [1,4]. So far, there is no proven intervention for treating or preventing the common cold. Thus, current treatments mainly focus on symptom relief. Few available therapies, including zinc, vitamin C, *Echinacea*, garlic, antihistamines, intranasal ipratropium, corticosteroids, antibiotics, and so on [5-14], are recommended due to ineffectiveness, questionable benefit, or adverse effects. Traditional Chinese Medicine (TCM) is a unique and well-established system of medicine that has benefited numerous people worldwide. In fact, in China and many other countries, a number of patients prefer TCM treatment rather than Western medicine to treat the common cold. As the most important component of TCM, Chinese medicinal herbs are mainly derived from plants and usually incorporate one or more herbs to treat a disease. Based on TCM syndrome differentiation, the common cold can be divided into the wind-cold, wind-heat or summer-heat dampness syndrome according to its symptoms and TCM signs, such as fever, headache, fatigue, aversion to cold, sneezing, nasal congestion, nasal discharge, nausea, vomiting, tongue proper, tongue coating and condition of pulse [15]. The common cold with wind-heat syndrome (CCWHS) is the most common type and occurs in all seasons; it is primarily characterized by fever, mild aversion to cold, sore throat, nasal congestion and discharge. According to the treatment principles of TCM, CCWHS should be treated by clearing heat and releasing stagnated *Lung-Qi*.

Gantong Granules is a novel Chinese patent medicine that is manufactured by Beikelian Pharmaceutical & Technology Co., Ltd, Shenzhen, China. It is mainly composed of *Chaihu* (*Radix bupleuri*), *Gegen* (*Radix puerariae*), *Niubangzi* (*Fructus arctii*), *Bohe* (*Herba menthae*), *Banlangen* (*Radix isatidis*), *Chuanbeimu* (*Bulbus fritillariae unibracteatae*), *Qianhu* (*Radix peucedani*) and *Jiegeng* (*Radix platycodi*). All of these ingredients have been approved by the China Food and Drug Administration (CFDA). Gantong Granules has been proven effective in treating CCWHS based on clinical experiences in the Affiliated Hospital of Changchun College of TCM. Preclinical pharmacologic experiments showed that Gantong Granules had the effects of clearing heat, relieving pain, reducing inflammation and alleviating cough. A second-stage clinical trial also demonstrated that it could improve symptoms of CCWHS. In addition, no evidence of an adverse or toxic effect has been found in toxicological studies.

In accordance with the Drug Administration Law of the People’s Republic of China and *Good Clinical Practice* (GCP) issued by CFDA, this phase IIb clinical trial is well-designed to evaluate the efficacy and safety of Gantong Granules compared with placebo in patients with CCWHS. Additionally, it is expected to find a dose-effect relationship and provide useful evidence for a Phase III clinical program.

## Methods/Design

### Design

This study is a multicenter, phase IIb, double-blind, placebo-controlled and randomized clinical trial. This trial has been authorized by the CFDA (Approval Number 2004 L04586) and registered with the Chinese Clinical Trial Registry (ChiCTR-TRC-14004255). In addition, the protocol is conducted in accordance with the *Declaration of Helsinki* (2008) and the *Good Clinical Practice* G*uidelines* [16]. The study is financially supported by Beikelian Pharmaceutical & Technology Co., Ltd, Shenzhen, China, which had or will have no role in the study design, analysis, data interpretation or decision to submit results. Across the five trial centers, all investigators are appropriately qualified by training and experiences to conduct and supervise the trial. All patients have to provide their written informed consent prior to study entry. The flow chart of this study is shown in Figure 1.

**Figure 1 Fig1:**
[figure not shown]
Study flow chart.

### Ethics

The trial protocol has been approved by five local ethics committees, including the Clinical Trials and Biomedical Ethics Committee of West China Hospital of Sichuan University (Number TCM-2013-08), the Clinical Trials and Biomedical Ethics Committee of the Affiliated Hospital of Chengdu University of TCM, the Clinical Trials and Biomedical Ethics Committee of the First Hospital of Hunan University of TCM, the Clinical Trials and Biomedical Ethics Committee of the Affiliated Hospital of Nanjing University of TCM, and the Clinical Trials and Biomedical Ethics Committee of the Affiliated Hospital of Jangxi University of TCM. Research assistants will introduce the trial to potential subjects, and give them information sheets about the trial. All eligible patients have to give their signed informed consent before enrollment. The privacy of all participants will be protected. Personal medical records will be taken by investigators and inspectors, who will promise to keep that secret. Regulatory authorities have the right to examine the test data. Data anonymity will be used in process of data management. Finally, the data of all subjects will be kept centrally.

### Recruitment

We plan to recruit patients through advertisements and recommendations. A total of 240 patients will be recruited in this trial at the following 5 hospitals across China: 1) West China Hospital of Sichuan University, 2) the Affiliated Hospital of Chengdu University of TCM, 3) The First Hospital of Hunan University of TCM, 4) the Affiliated Hospital of Nanjing University of TCM, 5) the Affiliated Hospital of Jangxi University of TCM. Forty-eight patients will be recruited at each center.

### Randomization and blinding

Using a stratified block randomization method, 240 eligible patients will be randomly allocated to the high-dose group, medium-dose group, low-dose group or placebo control group in a 1:1:1:1 ratio. The randomization sequence will be generated using the PRCO PLAN function of the analysis system of SAS software (SAS, Cary, NC, USA). The randomization lists will be concealed in a lightproof sealed envelope. The sealed envelopes will be kept by the leader and the sponsor of the study. Treatment allocation will be blinded to the participants and investigators throughout the course of the study. The emergency envelope will be saved in each center, and only be opened for medical emergency purposes.

### Diagnostic criteria for the common cold

The diagnosis in Western medicine is established according to *Practice of Internal Medicine* (2009, Version 13) [17] and *Consensus on the Diagnosis and Treatment of Common Cold by Respiratory Branch of Chinese Medical Association and Emergency Branch of Chinese Medical Association* [18]. Patients should have typical clinical manifestations of the common cold, such as sneezing, nasal discharge, nasal congestion, and/or sore throat, as well as excluding other diseases.

The TCM diagnosis of CCWHS is based on the *Guidelines for Clinical Research of New Chinese Medicine* [19]. The TCM diagnostic criteria for CCWHS are listed in Table 1. To be diagnosed with CCWHS, patients should have all the primary symptoms and at least three of the secondary symptoms, as well as the TCM signs for the tongue and pulse.

**Table 1 Tab1:** **Traditional Chinese Medicine (TCM) diagnostic criteria**

**Category**	**Symptoms and signs**
Primary symptoms	Fever, mild aversion to cold, sore throat
Secondary symptoms	Sore limbs, nasal congestion, nasal discharge, thirsty, cough
Signs for the tongue	Red tongue and thin yellow tongue coating
Signs for the pulse	Floating and rapid pulse

### Inclusion criteria

Diagnosis of common cold according to Western medicineDiagnosis of CCWHS according to TCMAged between 18 and 65 yearsPresenting within 48 hours after symptom onsetWilling to participate and sign the informed consent

### Exclusion criteria

Patients with influenza, acute bacterial sinusitis, allergic rhinitis, streptococcal pharyngitis and herpanginaPatients with imaging manifestations of pulmonary infectionPatients with serious primary diseases of the cardiovascular, pulmonary, kidney, and hematological systemPatients with liver function levels (such as alanine aminotransferase (ALT), aspartate aminotransferase (AST), serum total bilirubin (STB), alkaline phosphatase (ALP), and/orγ-glutamyl transpeptidase (γ-GT)) 1.5 times higher than the upper limit of normal, abnormal serum creatinine, positive urine protein qualitative test, white blood cell count < 3.0 × 10^9^/L or > 10.0 × 10^9^/L, and/or neutrophil percentage > 80%.Patients who are taking any medication to relieve symptomsPatients with a body temperature higher than 38.5°CPregnant women, lactating women, or women who have a birth planPatients with an allergic constitution or being allergic to the study drugMentally or legally disabled patientsPatients who are participating in or have participated in another drug clinical trial within the last 3 monthsPatients who have been judged by the investigator as inappropriate to participate in the clinical trial.

### Rejection criteria

MisdiagnosisNot taking any study drug during the trialUsing forbidden drugs or treatments during the trialNo evaluable records after drug administration

### Withdrawal criteria

Worsening conditions during the trial, including a body temperature higher than 39.0°CExperiencing anaphylaxis or serious adverse events during the trialQuitting the clinical trial voluntarilyThe study drug is not taken as directed, or is taken at doses <80% or >120% of the requirement

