### Interventions

Gantong Granules and placebo are provided and manufactured by Beikelian Pharmaceutical & Technology Co., Ltd, Shenzhen, China. Considering the characteristics of Chinese herbal medicine, placebo is prepared by 10-fold dilution of 5 g of Gantong Granules and then condensed into granules. The minimum effective dose of Gantong Granules is 5 g. After 10-fold dilution, the placebo will not have any clinical or pharmacological effects. Placebo is almost identical to the test drug in appearance, smell and taste. This preparation of placebo has been used in herbal medicine trials in China and Japan. All drugs are concealed in uniform packages with the same labels and each package contains 5 plus 1 days’ dosage. Patients in the high-dose group, medium-dose group, low-dose group or placebo control group, will receive Gantong Granules 15 g, Gantong Granules 10 g plus placebo 5 g, Gantong Granules 5 g plus placebo 10 g or placebo 15 g, respectively. All drugs will be dissolved in 200 ml warm water and taken orally before each meal 3 times daily for 3 to 5 days. If all symptoms disappear within 3 days, the study drugs should be taken for just 3 days; if not, for 5 days. During the study, patients will be visited five times by the investigators. The follow-up visits last for 7 days after the treatment. Details of study procedures are shown in Figure 2.

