### Outcome measures

#### Primary outcomes

The primary outcome of the study is the duration of all symptoms, which is defined as the number of hours from study enrollment to the time when the patient’s illness symptoms completely resolve. Each participant will be instructed to record any changes in symptoms in the patient diary, in which the data can be acquired. Investigator will make an assessment of the duration based on these data.

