### Statistical analysis

The data analysis will be performed by professional statisticians, in accordance with the statistical analysis plan for this trial. The full analysis set (FAS) is the primary analysis set for efficacy with an intention-to-treat (ITT) principle. In the FAS, all patients will be treated with at least one dose of the study drug and recorded with at least one clinical observation in the study. All subjects without any major protocol deviations will be involved in per-protocol set (PPS). The safety analysis will be conducted for randomized subjects who have completed at least one study visit and have safety data. Descriptive statistics will be performed on continuous variables, frequencies and categorical variables. All symptom duration, primary symptom duration, time to fever relief and time to fever clearance will be estimated by the Kaplan-Meier technique and be compared by the stratified log-rank test. Comparisons among groups will be conducted by an analysis of variance (ANOVA) and least significant difference*t*-test. In this multicenter trial, the Cochran-Mantel-Haenszel test, stratified by clinical centers, and the logistic regression model, adjusted for covariates, will be used. All data will be processed by a professional statistician using SAS 9.2 software (SAS, Cary, NC, USA), and a 2-sided *P*-value of < 0.05 is considered to be statistically significant.

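### Poor adherence to study drug is a ground for withdrawal, although the primary analysis follows intention to treat; if withdrawal ends follow-up, non-adherent patients who are still ill are censored on the primary outcome

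*Protocol article*

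**What the plan says.** Under Withdrawal criteria, one item applies when the "study drug is not taken as directed, or is taken at doses <80% or >120% of the requirement". It stands beside worsening illness, serious adverse events and a patient's own decision to leave.

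Under Statistical analysis, "The full analysis set (FAS) is the primary analysis set for efficacy with an intention-to-treat (ITT) principle". Patients enter that set if they were "treated with at least one dose of the study drug and recorded with at least one clinical observation in the study"; no adherence threshold is attached. The same section has a second set: "All subjects without any major protocol deviations will be involved in per-protocol set (PPS").

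The primary outcome is "the number of hours from study enrollment to the time when the patient"'s symptoms have fully resolved. It is taken from the patient diary and compared by Kaplan-Meier and a stratified log-rank test. Dosing is three times daily, and its length depends on recovery: "If all symptoms disappear within 3 days, the study drugs should be taken for just 3 days; if not, for 5 days". After that, "The follow-up visits last for 7 days after the treatment".

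**The concern.** An adherence rule of this kind normally defines a per-protocol set. Here it is a rule of conduct, and it can act on patients whom the ITT analysis needs to observe until they recover. The article does not say what withdrawal entails, and there are two readings:

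- **Withdrawal ends follow-up.** The heading, and the neighbouring item on leaving voluntarily, point this way. Adherence then decides how long the primary outcome is observed, and a patient in breach who is still ill is censored for it.
- **The item is a compliance count after treatment.** It is then a per-protocol criterion under the wrong heading.

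The first reading has a statistical cost. Kaplan-Meier uses the time up to censoring, so underuse unrelated to recovery loses events without bias. Underuse related to recovery makes the censoring informative, in a direction that the article does not fix.

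**Working it through.** **Planning figure.** Sample size calculation gives mean 7 days, SD 3, a 2-day reduction, 90% power and two-sided α = 0.05. n = 2 × (1.960 + 1.282)² × 3² / 2² = 47.3, so 48 per group; 48 / 0.80 = 60; 4 × 60 = 240. All three stated numbers reproduce.

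**Who can be caught by the percentage limits.** The two courses are 3 × 3 = 9 and 5 × 3 = 15 doses.

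| Course | Below 80% | Above 120% |
|---|---|---|
| 9 doses | 7/9 = 78% | 11/9 = 122% |
| 15 doses | 11/15 = 73% | not reachable from one package |

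Interventions says "each package contains 5 plus 1 days" of dosage, so 6 × 3 = 18 doses, and 18/15 is exactly 120%. Patients on the 9-dose course have already recovered, so their primary event is recorded. For the percentage limits, the exposure is therefore underuse on the 15-dose course. The other limb, drug not taken as directed, has no threshold. It can apply on any day and is not covered by the figures below.

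**Assumptions.** Withdrawal ends follow-up at day 5. Others are followed to day 12 (5 + 7). Durations are normal, N(7, 3) on placebo and N(5, 3) on active. The underuse rate u is the share of 15-dose patients; the article gives no such rate.

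**Still ill at day 5 among 15-dose patients,** P(T>5)/P(T>3):
- placebo: 0.748/0.909 = 0.82
- active: 0.500/0.748 = 0.67

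Gamma or log-normal durations give 0.77 or 0.75 on placebo and 0.59 or 0.53 on active.

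**Random underuse.** Censored while ill, per 60 = 60 × u × P(T>5). Events lost by day 12 = 60 × u × [P(T>5) − P(T>12)], with P(T>12) = 0.048 and 0.010. Full follow-up would give 57.1 + 59.4 = 116.5 events.

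| u | Censored while ill (placebo, active) | Events lost | Share of 116.5 |
|---|---|---|---|
| 5% | 2.2, 1.5 | 2.1 + 1.5 | 3% |
| 10% | 4.5, 3.0 | 4.2 + 2.9 | 6% |
| 20% | 9.0, 6.0 | 8.4 + 5.9 | 12% |

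Four missed doses can settle a breach before day 5. If everyone in breach were censored at day 3, the 20% row would become 60 × 0.20 × 0.909 = 10.9 and 60 × 0.20 × 0.748 = 9.0 patients.

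**Underuse related to recovery.** Kaplan-Meier medians, simulated with 400,000 per arm:

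| Pattern among 15-dose patients | u = 10% | u = 20% |
|---|---|---|
| Full follow-up (no censoring for underuse) | 1.99 | 1.99 |
| Ill beyond day 7 underuse twice as often | 1.93 | 1.81 |
| Recovered by day 7 underuse twice as often | 2.10 | 2.21 |

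The restricted mean difference to day 12 stays at 1.88-1.94 in these patterns, against 1.89 with full follow-up. Extreme patterns at 20%, with 36-73% of one recovery group underusing, give median differences of about 1.5 or 2.9 days. If every underuser had recovered between days 3 and 5, nothing would be lost.

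**The planned test.** Simulated unstratified log-rank, 60 per arm: power is about 91-92% without underuse and about 89-91% at 20% underuse, across the random and both two-fold patterns. With no treatment effect and the same pattern in both arms, rejection stays near 5%.

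**Arm-differential withdrawal.** This was simulated with no true effect, gamma durations and slower-than-average resolvers withdrawn between days 1 and 5. With 40% of them withdrawn in one arm and none in the other, rejection is about 14-16% if they are censored and about 5% if they are followed. At 40% against 10% it is about 11% and 6%.

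**The case against.** The strongest reply is that the harm rests on something the article leaves open. Follow-up after withdrawal may be set out in the full protocol. The list itself is ambiguous: a temperature above 39.0°C is also a withdrawal criterion, yet the section on concomitant treatments still calls such a patient a participant and allows cooling or paracetamol. Meeting a criterion therefore need not mean leaving observation. A withdrawn patient also still meets the FAS definition, the loss taken alone lies within the 20% drop-out allowance, and the effect on the planned test is a point or two of power.

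Most of this stands, and it keeps the priority low. What remains is that the article does state the placement: non-adherence is a ground for withdrawal. On the ordinary meaning of the word, following that rule costs primary-outcome follow-up. A later analysis plan cannot recover it, because Data management has that plan made at blind review, after the case report forms are in. The drop-out allowance replaces lost numbers, is shared with other losses, and does not correct informative censoring.

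A reader might go further and infer that non-adherent patients are removed from the FAS, or that the rule inflates the false-positive rate. The documents support neither. The FAS definition has no adherence condition. False positives rise only if the link between underuse and recovery differs strongly between arms, and nothing in a double-blind trial with closely matched granules gives a basis for assuming that.

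**Conclusion.** The point holds in conditional form. The whole adherence item is misplaced among the withdrawal criteria, given an ITT-based primary set and an existing per-protocol set. If withdrawal ends follow-up, the likely cost is modest: a loss of events and a little power, with bias only where underuse tracks recovery, in either direction. These sizes rest on assumed underuse of 5-20%, normal durations at the planning values and censoring at day 5. They leave out the limb without a threshold and would be larger with earlier censoring. No stated number is wrong. Minor to moderate priority.

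**What to change.** Remove the entire item from Withdrawal criteria, both the as-directed limb and the 80%-120% limits, and make it an exclusion from the per-protocol set, measured against the prescribed 9 or 15 doses. Moving only the percentage limits would leave the limb without a threshold as a ground for withdrawal.

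Add that such patients stay in the trial, keep the symptom diary until symptoms resolve or the 7-day follow-up ends, and are analysed in the FAS.

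The cost is two sentences and continued diary collection from non-adherent patients. No visit or measurement is added, and the sample size need not change.
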